## Introduction

*Clostridioides difficile* (also known as *Clostridium difficile*) infections (CDI) are linked to extended hospital stays and fatalities, particularly in the elderly population [1]. Though CDI is considered a nosocomial infection, community-based transmission among older adults is common [2]. An increase in CDI incidence has been observed in American, European, and certain Asian hospitals over time. This tendency can be attributed to the increasing antibiotic usage and the emergence of novel, hypervirulent strains [3-6]. In parallel with the rising CDI incidence, the antibiotic resistance pattern and associated mortality have also increased [7].

*Clostridioides difficile* (CD) usually spreads by the fecal-oral route and causes exotoxin-mediated illness. In India, CDI affects 3.4-18% of people, with older adults having a greater risk [8]. While 3-15% of healthy persons may have CD in their normal flora, 16-35% of hospitalized patients may have asymptomatic colonization [9,10]. The most significant risk factor for CDI is the use of antibiotics. The antibiotic class and its exposure duration determine the infection likelihood [11].

The resistance of the bacterial spores to heat and disinfectants contributes to the spread of CDI in hospitals. CDI ranges from mild diarrheal symptoms to fatal colitis [3,12]. Nowadays, community-acquired colitis is more prevalent owing to CDI and infective diarrhea [12]. Recurrent CDI (rCDI) increases morbidity, mortality, and healthcare costs and dampens the quality of life [3,12,13]. A recent meta-analysis shows 8.3 CDI cases for every 10,000 patient days [13]. Complex carbohydrate conversion by the normal colonic microbiota is essential to elicit resistance to invading microorganisms [14]. Gut microbiomes digest complex carbohydrates, starch, and dietary fiber to create short-chain fatty acids (SCFAs). SCFAs modulate inflammation and the immune system by lowering T and B cell differentiation and migrating immune cells (i.e., neutrophils, dendritic cells, and macrophages) [15].

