The CD colonization status will be documented by culture of stool or rectal swabs collected on days 0 and 15. The stool or rectal swab samples will be subjected to glutamate dehydrogenase (GDH) and toxin assay (by enzyme immunoassay, EIA) tests for the participants with suspected CDI. The samples positive for GDH and/or toxin shall be subjected to a nucleic acid amplification test (NAAT). In confirmed cases of CDI, culture for CD (using selective media and anaerobic gas pack) shall be done. The positive culture isolates shall be subjected to VITEK-2 for antimicrobial susceptibility testing (AST). The sample aliquots shall be stored at -80°C for further analysis.

The CD-positive isolates from 30 participants (10 each of those who acquired CD, who eliminated CD, and who had confirmed CDI) shall be subjected to whole genome sequencing. The fecal cytokines (e.g., CXCL-5, CXCL-8) and lactoferrin shall be estimated by enzyme-linked immunosorbent assay (ELISA) kit in a subset of 25 participants per group from stool or rectal swab samples collected on days 0 and 15. The *Torani* product samples will be cultured to detect microbiota (e.g., *Lactobacillus* species), followed by the bacteria species identification (16S rRNA gene amplification) and analysis of SCFAs by high-performance liquid chromatography (HPLC).

Statistical analysis

Sample Size Calculation

A study documented that probiotic consumption reduced CDI by approximately 70% [27]. Assuming that the *Torani*-xylitol mix shall reduce the CD colonization from 15% to 5% in hospitalized participants at discharge, the estimated sample size is 196 participants (98 per group) with a 95% confidence level and 80% power. Thus, we propose to include 200 participants (100 per group).

Data Analysis

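### The stated 80% power is not reached with 100 per group at 15% versus 5% colonisation, and the assumed reduction rests on an infection effect, not a colonisation effect

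*Protocol article*

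**What the plan says.** The Sample Size Calculation (Materials and methods, Statistical analysis) opens with its evidence for the effect: "A study documented that probiotic consumption reduced CDI by approximately 70" per cent. It then moves to another endpoint: "Assuming that the *Torani*-xylitol mix shall reduce the CD colonization from 15% to 5% in hospitalized participants at discharge". From this it derives 98 per group (196 in total) at 95% confidence and 80% power, and plans 100 per group. It gives no source for the 15%, no source for an effect on colonisation, and does not say whether the test is one- or two-sided.

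The Introduction gives two colonisation ranges: "While 3-15% of healthy persons may have CD in their normal flora, 16-35% of hospitalized patients may have asymptomatic colonization". The trial enrols hospitalised patients over 60, and the comparator is plain water. Among the limitations, the Discussion says that an exact power analysis was not possible because no earlier study of this product exists.

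**The concern.** Three features of the paragraph do not fit together.

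- The control rate equals the top of the article's range for healthy persons and falls just short of its range for the kind of patient enrolled.
- The effect behind the calculation was seen on infection, while the trial is sized on colonisation. Carriers on admission are not excluded, and the sequencing plan expects some participants to clear the organism ("10 each of those who acquired CD, who eliminated CD, and who had confirmed CDI"). Colonisation at discharge can therefore include carriage present at entry, and a given fall in disease does not imply the same fall in that proportion.
- The 80% is the only power figure in the article. If it is too high for the stated scenario, and the scenario has no evidence on the right endpoint, a reader has no sound statement of which effects 200 participants can detect.

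**Working it through.** **Inputs.** From the Sample Size Calculation: p1 = 0.15, p2 = 0.05, power 80%, 98 per group estimated, n = 100 per group planned. From the Data Analysis section: chi-square or Fisher's exact test, significance at p < 0.05. From the Introduction: 16% and 35% as the ends of the hospitalised range. My assumptions: a two-sided test, 25% as an intermediate control rate, and 50% as a weaker reduction. The last is illustrative and is not in the article.

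**Step 1: the plan's own figure.** With pooled variance under the null and m the mean of p1 and p2,

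n per group = [1.96·√(2m(1−m)) + 0.842·√(p1(1−p1) + p2(1−p2))]² / (p1−p2)²

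For 0.15 and 0.05, m = 0.10, √0.18 = 0.424 and √0.175 = 0.418. So n = (0.832 + 0.352)² / 0.01, about 140, which is 141 at full precision and rounded up.

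Other standard variants give 138 (unpooled), 133 (arcsine), 160 (continuity-corrected) and 111 (one-sided). None gives 98. Two routes do reach the stated size: a one-sided 5% test of 15% against 4.5%, an exact 70% cut (98 per group), and the precision formula for one proportion, 1.96² × 0.15 × 0.85 / 0.05² = 195.9 in total. The article states neither, so I do not attribute either to it.

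**Step 2: power of 100 per group for the stated scenario.**

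Power = Φ{[(p1−p2)·√n − 1.96·√(2m(1−m))] / √(p1(1−p1) + p2(1−p2))}

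- 15% v 5%: (1.000 − 0.832) / 0.418 = 0.403, so power is 66% (65% with 98 per group; 76% if one-sided with 100).
- 16% v 5.3%: (1.067 − 0.856) / 0.430 = 0.491, so power is 69%.

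**Step 3: the same formula over the article's hospitalised range.** The assumed relative reduction is (15 − 5)/15 = 67%, or two thirds.

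| Control rate | Two-thirds reduction | 50% reduction |
|---|---|---|
| 15% | 66% | 39% |
| 16% | 69% | 41% |
| 25% | 89% | 62% |
| 35% | 98% | 81% |

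With a two-thirds reduction, power reaches about 80% at a control rate of 20% (79.7%). With a 50% reduction, it passes 80% only near the top of the range. Carrying the cited 70% over to colonisation in full still gives only 71% at a 15% control rate and 74% at 16%.

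**Step 4: what 100 per group can detect with 80% power.** The required relative reduction is about 76% at a 15% control rate, 74% at 16%, 60% at 25% and 50% at 35%.

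**The case against.** **The control rate.** The gap to the hospitalised range is one point, and that range is itself worded tentatively. Moving from 15% to 16% at the same relative reduction changes power by three points, upwards. The article's rationale is a relative reduction, and on that scale 15% is the cautious choice. This stands in full. A reader might infer that the low control rate undermines the sizing; the calculations show the opposite.

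**Power falling as the control rate rises.** Holding a 10-point absolute difference gives 62%, 42% and 34% power at 16%, 25% and 35%. At 35%, though, 10 points is only a 29% relative reduction, far from the effect that the article cites. Nothing in the article supports a fixed absolute difference across control rates.

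**An effect on new acquisition only.** A reader might suppose that the product prevents acquisition but leaves existing carriage untouched, and obtain very low power. That needs an entry carriage rate for these patients, which the article does not give, and it assumes that no carrier clears the organism, although the plan expects some to do so. It is no basis for a figure here.

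**Disclosure.** The reduction is already introduced as an assumption, CDI is named as the outcome of the cited study, and the Discussion admits that the power analysis is limited. This stands in part and lowers the weight of the point. But the paragraph puts the CDI result forward as its only support without saying that the endpoint differs, and the 80% carries no qualification.

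**Interpreting a null result.** The Data Analysis section promises risk differences and risk ratios with 95% confidence intervals, which will show the effects still compatible with the data. So it would be too strong to say that a null result could not be interpreted.

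**Conclusion.** The point holds in a limited form. The stated 80% power is not what 100 per group delivers for 15% against 5%: it is 66% at two-sided 5%, and 69% at the lower end of the article's own hospitalised range. The two-thirds reduction has no cited support on colonisation; its only backing is an effect on CDI. If colonisation fell by half instead, power would be 39% at 15% and 41% at 16%.

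The control rate alone is not a fault. If true colonisation lies in the middle or upper part of 16-35% and the two-thirds reduction is real, 100 per group is ample (89% at 25%, 98% at 35%).

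These figures assume a two-sided 5% test, the normal approximation and all 100 per group analysed. A one-sided reading gives 76% for the stated scenario, still below 80%. The documents contain no colonisation effect, so the true power cannot be fixed, only shown as a range.

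**What to change.** Keep 200 participants and rewrite the sizing paragraph.

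1. Replace the single 80% with the table in step 3: power of 100 per group at control rates of 15%, 16%, 25% and 35%, for a two-thirds and a 50% reduction, labelled as two-sided 5%.
2. State that the reduction in colonisation is an assumption without direct evidence, and that the cited 70% refers to CDI.

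The cost is one reworded paragraph and a four-row table, with no extra patients or samples. By the article's own account the trial has not started, so the change can be made before any data exist. The downside is that a single reassuring figure becomes a range that includes values below 80%. The change does not raise power; it states which effects the planned size can and cannot detect.

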The normality of the data distribution will be gauged using the Shapiro-Wilk test. The continuous variables will be expressed as mean and standard deviation or median and interquartile range based on the distribution pattern. The categorical variables will be expressed as frequency and proportion. Missing data will be addressed using various imputation techniques, and sensitivity analyses will be conducted to assess the robustness of the results. The quantitative data with normal distribution will be compared using the unpaired t-test, and those with skewed distribution will be analyzed using the Mann-Whitney U test. The categorical data will be compared using the chi-square or Fisher's exact test, as applicable. Analysis of variance (ANOVA) or the Kruskal-Wallis test shall be considered for the multiple comparisons. A p-value of < 0.05 will be considered significant. For the study outcomes, results will be summarized in absolute (risk difference or mean difference) and relative (risk ratio) effect size measures along with their 95% confidence intervals. Regression analysis shall be done to identify the factors that influence CD colonization or infection and their strength of association. A per-protocol (PP) analysis will be performed to assess efficacy. The safety analysis will be done using the intent-to-treat (ITT) principle. R software (version 4.5.0 or higher) will be used for the data analysis and generation of plots [28].

Interim Analysis

One interim analysis is proposed after enrollment of 50% (n = 100) of participants and completion of the day-15 data. The interim analysis will be conducted using the O’Brien-Fleming spending function and a type I error rate of 5%.

Ethical Consideration and Trial Registration

The Institutional Ethics Committee of KIMS, Bhubaneswar, has approved the study protocol (KIIT/KIMS/IEC/1753/2024). The trial has been prospectively registered with the Clinical Trial Registry of India (CTRI/2025/03/083479). The study will comply with the Good Clinical Practice (GCP), the Declaration of Helsinki, and institutional norms. All the participants will be recruited for the study after obtaining written informed consent, and their privacy and confidentiality will be maintained.

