## Discussion

This RCT has been designed to document the effect of the *Torani*-xylitol mixture on CD colonization and CDI by modulating gut microbiota among hospitalized elderly patients. The outcome measures are CD colonization, CDI incidence, CD profile (genotype, phenotype, and AST) of CD, and safety of the investigational product. As gut dysbiosis is an important causative factor for CDI, the probiotic-prebiotic-synbiotic products have potential roles [11,14]. The traditional probiotic-rich foods like *Torani* (fermented rice water) in Odisha provide advantages in their acceptability, ease of preparation, availability and use, and affordability. The components of *Torani*, like SCFA and enrichment with prebiotic (xylitol), are likely to repair gut dysbiosis, modulate colonic milieu, improve gut immunity, and prevent CD colonization and CDI [14,15,17,19].

This study has a few limitations. First, the study design is an open-label RCT, owing to the nature of the intervention. Allocation concealment will be done to mitigate the performance and detection bias. Second, the duration of therapy is fixed for all participants irrespective of the group, gender, disease, or hospitalization duration. Third, we could not get the exact power analysis for this study, as this is the first study to document the effect of the *Torani*-xylitol mixture on CD colonization and CDI.

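### The stated inputs (15% v 5%, 95% confidence, 80% power) do not give 98 per group; the planned 100 per group has about 66% power

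*Protocol article*

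**What the plan says.** The Sample Size Calculation (Protocol article, Materials and methods) opens with the source of the effect: "A study documented that probiotic consumption reduced CDI by approximately 70"%. It then assumes that the product will "reduce the CD colonization from 15% to 5% in hospitalized participants at discharge", and reports that "the estimated sample size is 196 participants (98 per group) with a 95% confidence level and 80% power". The total is taken up to 200, 100 per group, with no stated allowance for loss.

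The Data Analysis section sets the test: "The categorical data will be compared using the chi-square or Fisher's exact test, as applicable". The threshold is "A p-value of < 0.05 will be considered significant", and effects are to be given as risk differences and as "relative (risk ratio) effect size measures along with their 95% confidence intervals". Neither section states whether the test is one- or two-sided, and no one-sided test is mentioned anywhere.

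**The concern.** The article gives every input needed to check the sample size except sidedness, and the answer is well below what the usual formula returns. This is the trial's only sample size justification. If the true power is near two in three, a non-significant result at the assumed effect is much more likely than the 80% figure suggests, and readers could take it as evidence that the product does not work. The trial has not started, so the statement can still be corrected before any data exist.

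**Working it through.** **Inputs.** p1 = 0.15 and p2 = 0.05 (Sample Size Calculation); alpha = 0.05 (95% confidence level; p < 0.05); power 80%, so z_b = 0.8416; 1:1 allocation; planned n = 100 per group. Sidedness is not stated, so both are tried: z_a = 1.9600 (two-sided) and 1.6449 (one-sided).

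**Formula (pooled variance under the null).** n per group = [z_a·√(2·p̄·q̄) + z_b·√(p1q1 + p2q2)]² / (p1 − p2)²

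**1. Stated inputs, two-sided.** p̄ = 0.10, 2·p̄·q̄ = 0.18, p1q1 + p2q2 = 0.1275 + 0.0475 = 0.175.
n = (1.9600 × √0.18 + 0.8416 × √0.175)² / 0.10² = (0.8315 + 0.3521)² / 0.01 = 140.1, so **141 per group**.
Unpooled: (1.9600 + 0.8416)² × 0.175 / 0.01 = 137.4, so **138**.

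**2. Stated inputs, one-sided.** n = (0.6979 + 0.3521)² / 0.01 = 110.2, so **111 per group**.

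**3. Other formulas for 15% v 5%, n per group.**

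| Formula | Two-sided | One-sided |
|---|---|---|
| Pooled | 141 | 111 |
| Unpooled | 138 | 109 |
| Pooled under both hypotheses | 142 | 112 |
| Arcsine | 133 | 105 |
| Continuity-corrected | 160 | 130 |

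None gives 98.

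**4. Where 98 can come from.** A 70% reduction from 15% gives 15% × 0.30 = 4.5%. Then p̄ = 0.0975, 2·p̄·q̄ = 0.1760, p1q1 + p2q2 = 0.1705, difference 0.105.
One-sided: n = (0.6900 + 0.3475)² / 0.105² = 97.6, so **98**, an exact match.
Two-sided with the same rates: 124.1, so 125.

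**5. Power with 100 per group.** Power = Φ{[√n·(p1 − p2) − z_a·√(2·p̄·q̄)] / √(p1q1 + p2q2)}
- 15% v 5%, two-sided: Φ[(1.0000 − 0.8315) / 0.4183] = Φ(0.403) = **65.6%** (unpooled 66.7%).
- 15% v 5%, one-sided: Φ[(1.0000 − 0.6979) / 0.4183] = Φ(0.722) = **76.5%**.
- 15% v 4.5%, two-sided: 70.9%.
- 15% v 5%, two-sided, exact binomial enumeration: uncorrected chi-square 68.3%, Fisher 58.6%.

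At 98 per group, two-sided power for 15% v 5% is 64.8%.

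**6. Illustration of loss (assumed, not from the article).** For 15% v 5%, two-sided, 90 evaluable per group gives 61.0% and 80 gives 56.0%.

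The planned interim analysis is not included in any of these figures.

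**The case against.** The strongest reply is that sidedness is never written down, and that a one-sided test with a 70% reduction reproduces 98 exactly. Both facts are right. But the article states 5%, not 4.5%, as the intervention rate, and for 15% v 5% even the one-sided test falls short. The match shows a possible origin of the number. It does not establish what was done, and it does not make the written statement correct.

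Three stronger readings are tempting and are not supported.

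- A reader might take the limitation in the Discussion, "we could not get the exact power analysis for this study", as contradicting the 80% claim. It does not. The stated reason is that this is the first study of the product, so it concerns missing prior data. A calculation on assumed rates is compatible with it. Equally, it does not explain an arithmetic mismatch.
- A reader might count deaths, referrals and early discharges as automatic losses. The Abstract makes discharge, death and referral sampling points, and Data Analysis plans imputation and sensitivity analyses. What does stand is that efficacy is to be assessed per protocol, and any exclusions from that set would lower power. The article gives no rate for this.
- A reader might quote the Fisher figure (about 59%) as the trial's power. With average colonization of 10% and 100 per group, the smallest expected cell is 100 × 0.10 = 10, so by the usual expected-count convention the chi-square test would apply.

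It would also be unsafe to name one intervention rate at which 100 per group reaches 80%. The normal approximation puts it near 3.6%, the exact chi-square just below 4%, and neither rate has a basis in the article.

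**Conclusion.** Wrong as written. For 15% v 5% at 5% significance and 80% power, 98 per group is not reproduced under either sidedness by any of the formulas tried. On a two-sided test the requirement is 141 per group (138 unpooled), and the planned 100 per group gives about 66% power (68% by exact uncorrected chi-square). The chance of missing the target effect is thus about 34%, against the 20% implied.

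The 66% rests on a two-sided test, which is an inference from the chi-square or Fisher tests at p < 0.05 and the 95% confidence intervals. The conclusion that power is below 80% does not depend on that inference, since the one-sided figure is 76.5%. All these figures assume that all 100 per group are analysed.

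**What to change.** Restate the paragraph along these lines: *With 100 participants per group and a two-sided 5% test, power is about 66% to detect a reduction in colonization from 15% to 5%.* Remove the 80% claim for that effect. State the sidedness of the test and the intervention rate used, so that the 5% in the calculation and the cited 70% reduction (4.5%) are no longer left side by side unexplained. Any loss scenario added to the text should be marked as illustrative.

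The cost is wording only. The stated power becomes less favourable, and correcting the figure needs no change in enrolment. If the sponsor prefers to keep 80% power for 15% v 5%, the reference figure is 141 per group (282 in total) before any loss and before any adjustment for the interim analysis. That is a separate decision, still open because the trial has not started. The limitation in the Discussion needs no change on this account.

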## Materials and methods

Study design

This two-arm, open-label, randomized controlled trial (RCT) will be conducted at the Kalinga Institute of Medical Sciences (KIMS), Bhubaneswar, Odisha, India.

Participant and eligibility criteria

The patients aged above 60 years, of any gender, admitted to the hospital within the last 48 hours, anticipated to be admitted for at least seven days, and allowed orally or through the nasogastric tube will be included. The patients with known immunocompromised status (on high-dose steroids or immunosuppressants), scheduled for or who underwent any surgical procedure, on nil-per-oral (NPO) advice, admitted for only diagnostic tests or short-term assessment, requiring life support systems for unstable vitals, with renal failure or on fluid restriction, on any probiotics, with known food allergy or intolerance to xylitol, not complying with the study protocol, and very sick patients (death is thought to be imminent) will be excluded.

Study procedure

Investigational Product

The participants shall consume either of the two products under supervision. The products shall be prepared daily in the kitchen, packaged in similar bottles labeled with the participant ID, and supplied to the participants for daily consumption for up to 14 days.

Intervention Product

The participants in the intervention arm (Group A) shall receive the *Torani*-xylitol mixture containing 350 ml *Torani* (overnight fermented rice water prepared from cooked rice) and 5 gm xylitol once daily for up to 14 days. There is no prohibition on consuming the product with the meals.

Comparison Product

The participants in the comparator arm (Group B) shall be provided 350 ml of plain mineral water.

Randomization and Blinding

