After obtaining informed consent, the participants (a total of 200 in the two groups) will be randomized into either of the two groups in a 1:1 ratio, following computerized permuted block randomization with block sizes of 4 and 6 (generated by an independent biostatistician using a web-based random number generator). Allocation concealment will be done using double-layered opaque envelopes. After obtaining consent from the participant, the research staff will inform the independent nurse (who will have the envelopes for randomization) to open the envelope and identify the group allocation, assign the study ID sequentially as per the envelope, and inform the study team member. Once opened for a participant, the envelope will not be used for another participant, even if the participant declines participation subsequently. The used envelopes shall be submitted to the independent statistician.

After opening the sealed envelope and allocating the participant, the study team member will inform the product preparation team (PPT) about the study ID and allocation group for the supply of the study product. The study products shall be prepared daily, packed in similar bottles, labeled with the participant’s ID (neither group nor product mentioned), and supplied individually to the concerned participant’s bedside. The products (i.e., *Torani*-xylitol mixture or plain mineral water) shall be supplied in sealed bottles labeled with the study IDs of the participants to the respective participant’s bedside daily (morning hours). The participants shall be asked to consume these drinks within two hours of supply, and the bottles shall be collected.

Due to the nature of the products, the participants and research staff cannot be blinded. The laboratory analysis and outcome-assessing teams will be blinded to the study group allocation. The bottles shall be selected to minimize the visualization of the product. For any reason, if required, the investigation product may be stopped (temporarily or completely) as per the instruction of the treating doctor.

Data Collection and Follow-Up

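### The printed 80% power does not hold for the per-protocol efficacy analysis: 15% v 5% at two-sided 5% gives about 66% at 100 per group, and less after any exclusions

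*Protocol article*

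**What the plan says.** The Sample Size Calculation assumes that the mixture "shall reduce the CD colonization from 15% to 5% in hospitalized participants at discharge", and concludes that "the estimated sample size is 196 participants (98 per group) with a 95% confidence level and 80% power". It then rounds up: "Thus, we propose to include 200 participants (100 per group". It does not state the sidedness or the formula, and gives no allowance for loss.

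Randomization and Blinding confirms that the 200 are counted at allocation: "the participants (a total of 200 in the two groups) will be randomized into either of the two groups in a 1:1 ratio". Data Analysis sets the decision rule, "A p-value of < 0.05 will be considered significant", with a chi-square or Fisher's exact test for categorical outcomes. It names the efficacy analysis: "A per-protocol (PP) analysis will be performed to assess efficacy". Intention to treat is reserved for safety. The same section plans imputation and sensitivity analyses for missing data.

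**The concern.** The required number, the number randomised and the efficacy analysis set are all printed in this article, and they do not fit together. A per-protocol set is a subset of those randomised. With 100 randomised against a stated need of 98, the power claim has almost no room for exclusions. The claim is also unsupported before any exclusion, because 98 per group does not follow from the stated 15% and 5%.

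The stake is how a null result would be read. If colonisation does not differ significantly, readers will judge that finding against a stated 80% chance of detecting a drop to one third. The analysed set would have had a chance nearer 56% to 66%.

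**Working it through.** **Inputs.** Control rate p1 = 0.15, intervention rate p2 = 0.05, 95% confidence (5% significance), 80% power, 98 per group required and 100 per group randomised (Sample Size Calculation); 1:1 allocation (Randomization and Blinding). Sidedness is not stated. Two-sided is taken as the standard reading of a 95% confidence level with p < 0.05.

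**Step 1: try to reproduce 98 per group.** With p̄ = 0.10, the usual two-proportion formula (pooled variance under the null, unpooled under the alternative) is

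n = [z(α/2)·√(2·p̄·(1 − p̄)) + z(β)·√(p1(1 − p1) + p2(1 − p2))]² / (p1 − p2)²

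= [1.960·√0.18 + 0.842·√0.175]² / 0.01 = (0.8315 + 0.3521)² / 0.01 ≈ 140.1, so **141 per group** (282 in total).

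Other methods on 15% v 5% do not give 98 either:

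- Two-sided: 138 unpooled, 133 arcsine, 160 continuity-corrected.
- One-sided: 111 pooled, 109 unpooled, 105 arcsine.

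Two calculations on inputs other than those stated do reach the printed figures:

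- One-sided 5% with 15% v 4.5% gives 98 per group. The 4.5% is 15% × 0.30, from the 70% reduction in infection cited beside the calculation.
- A single-proportion precision formula, 1.96² × 0.15 × 0.85 / 0.05² = 195.9, gives 196 in total.

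Which of these was used, if either, cannot be told from the article.

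**Step 2: power at the number analysed.**

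Power = Φ{[(p1 − p2)·√n − z(α/2)·√0.18] / √0.175}

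At n = 100: Φ[(1.000 − 0.8315) / 0.4183] = Φ(0.403) = 65.6%. The other rows follow in the same way. The last column uses the one-sided inputs that return 98, for comparison only.

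| Analysed per group | Loss from 100 | 15% v 5%, two-sided 5% | 15% v 4.5%, one-sided 5% (not the stated inputs) |
|---|---|---|---|
| 100 | 0% | 65.6% | 80.8% |
| 98 | 2% | 64.8% | 80.1% |
| 90 | 10% (assumed) | 61.0% | 77.1% |
| 85 | 15% (assumed) | 58.6% | 75.0% |
| 80 | 20% (assumed) | 56.0% | 72.7% |

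Exact two-sided power at 100 per group, for the tests the plan names, is 68.3% with chi-square and 58.6% with Fisher's exact test. The approximation lies between them.

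**Step 3: separate the two shortfalls** (15% v 5%, two-sided).

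- Base calculation: 80.0 − 65.6 = 14.4 points, with nobody lost.
- Loss: 65.6 − 61.0 = 4.6 points at 10%; 65.6 − 58.6 = 7.0 at 15%; 65.6 − 56.0 = 9.6 at 20%.

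**Step 4: the margin.** 100 − 98 = 2 per group. Inflating 98 so that 98 remain after exclusions would restore only 64.8%, not 80%.

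**The case against.** The strongest reply is that this is only an unstated dropout allowance in a condensed article, and that several apparent losses are not losses on the text. Much of that stands:

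- **Discharge, death and referral.** The Abstract provides for a sample at each of these exits, and the sample size is set on colonisation at discharge. They are not certain losses.
- **Short courses.** Entry needs only a stay "anticipated to be admitted for at least seven days", but the product is given for up to 14 days, so a shorter course is not shown to be a protocol departure.
- **Stopped product.** The treating doctor may stop it. The article does not define the per-protocol set, which may be left to the analysis plan, so it is unknown whether those participants are excluded.
- **Spent envelopes.** The rule is that "the envelope will not be used for another participant, even if the participant declines participation subsequently". This bars reuse of an envelope; it does not say that further participants cannot be enrolled.
- **Loss rates.** The 10% to 20% range is an assumption with no source in the document.

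A reader might also infer that the 80% is sound up to a 2% loss and fails beyond it. The documents do not support that. On the stated rates, two-sided, the 80% already fails at zero loss. On the one-sided 15% v 4.5% inputs, going from 98 to 95 per group moves power only from 80.1% to 79.0%, and a loss just above 2% costs under 1 point. The 2% line has no practical meaning as a threshold.

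Two counter-arguments do not remove the point. Planned imputation may recover missing swab results, but it does not return participants excluded from a per-protocol set. The Discussion concedes that an exact power analysis was not possible because the mixture had not been studied before; that concerns the assumed effect, and the 80% is still printed for a stated effect.

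**Conclusion.** The point stands in this limited form: the stated 80% is not the power of the efficacy analysis that the plan names. The larger cause is the base calculation, which leaves about 66% at 100 per group with nobody lost (15% v 5%, two-sided 5%, normal approximation). The smaller cause is that efficacy is analysed per protocol with only 2 per group in hand. Exclusions cost about 5 points more at 10% and about 10 at 20%, giving about 61% and 56%.

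The first figure rests on a two-sided reading. A one-sided 5% test on 15% v 5% would give 76.5% at 100 per group, still short of 80%. The second rests on assumed loss rates, equal in both groups, with those excluded having the same colonisation rates as those kept. How many participants will be excluded cannot be established from the article. It would be wrong to attribute the whole gap between 80% and 56% to loss.

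**What to change.** In Sample Size Calculation:

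1. State the sidedness and the test on which the calculation rests.
2. Say that 200 (100 per group) is the number randomised, not the number analysed.
3. State the expected number per group evaluable per protocol for colonisation, with the reason for that figure. Do not count discharge, death, referral or a course shorter than 14 days as automatic losses.
4. Replace the 80% with the power at that number, and show the two shortfalls separately. For example: *With 100 per group and none excluded, power for 15% v 5% at two-sided 5% is about 66%; with 90 per group evaluable per protocol it is about 61%, and with 80 about 56%.*

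This takes a few sentences, and the Results section confirms that the study has not commenced. Enrolment can stay at 200. The cost is a less favourable stated power.
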